### 2.3. Sample Allocation Procedure and Allocation Concealment

All participants will be assigned to a single group, with the order of intervention randomly assigned through a one-group, five-arm randomization process known only to one researcher (Evaluator 1). This researcher will be responsible for delivering the order in which the three bottles, identified by stickers on the bottom, will be applied by the second researcher (Evaluator 2), who will be responsible for applying the intervention protocols and collecting data. These bottles, containing the oil corresponding to the allocation group, will be numbered 1 to 3. The contents of these bottles, identical in color and viscosity, will be known only to the researcher responsible for randomization (Evaluator 1), who will remain locked in a room throughout the data collection. After all stages of the intervention: 1-Pre-Intervention (PRE-IN); 2-Intervention (IN); 3-Post-Intervention (POST-IN)—the data collection will be assessed by the third researcher (Evaluator 3). Ensure allocation concealment and blinding of both participants and researchers.

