## 2. Materials and Methods

This is a randomized controlled crossover clinical trial with a 1:1:1 allocation ratio, double-blinded, which will be described according to the Consolidated Standards of Reporting Trials (CONSORT) criteria [21] where the checklist will be available in the online Supplementary Materials, and the protocol will follow the description suggested by the Standard Protocol Items Recommendations for Interventional Trials (SPIRIT) [22]. This study will be conducted at the Onofre Lopes University Hospital, of the Federal University of Rio Grande do Norte. The study was authorized by Brazilian Health Regulatory Agency (ANVISA) and was registered in the Brazilian Clinical Trials Registry—ReBEC, a public registry, under the trial registration number RBR-3jsvtbr, with the registration date of 30 April 2024.

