### 2.1. Sample Size and Allocation

The sample size will be determined after a pilot study with five subjects, considering the cardiac output (CO) values as the main variable in intra- and inter-group comparisons through mixed model analysis of the Generalized Estimating Equations (GEE) test. An alpha error of 0.05 with a two-sided distribution and a test power of 80% will be established. Recruitment will be done through convenience sampling, using direct invitations and advertising on social media, posters, flyers on Instagram and WhatsApp, targeting the general population.

Participants will be randomly assigned to a single group, which will undergo five different types of interventions: (1) CBD + THC intervention at 12.50 mg (CBD + THC/12.50 mg), (2) CBD + THC at 18.65 mg (CBD + THC/18.65 mg), (3) THC intervention at 12.50 mg (THC/12.50 mg), (4) THC at 18.65 mg (THC/18.65 mg), and (5) placebo intervention (IP). The order of interventions for each individual will be randomized using the https://www.sealedenvelope.com website for analysis (accessed on 4 September 2025).

To conduct the five research interventions, we will use three different oils. The first is an THC oil with a concentration of 2.50 mg/mL “Naternal Full Spectrum Delta 9 THC”, from (Naternal^®^, Morrisville, NC, USA). The second is a Cannabis oil containing 50 mg/mL CBD and 1.83 mg/mL THC “Lazarus Naturals High Potency Full Spectrum” from (Lazarus Naturals^®^, Seattle, DC, USA). The third, used in the placebo intervention (IP), is an MCT (Medium Chain Triglycerides) oil used as a base for diluting the full-spectrum Cannabis and THC oils, consisting of 70% fractionated coconut oil and 30% corn oil.

During the THC evaluations, the mL dosages will be determined based on the concentration of the product. Similarly, in the evaluations of the CBD + THC intervention, the THC and cannabis oils will be combined to achieve an equal ratio of CBD and THC for each specific dose. In the placebo intervention, all participants will receive a dose of 5.00 mL of MCT. The dosages and corresponding values are detailed in Table 1.

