**Figure 2 jcm-14-07531-f002:**
[figure not shown]
CONSORT 2025 Flow Diagram.

**Table 1 jcm-14-07531-t001:** This table summarizes the amount and type of substance used in each intervention arm of the research.

Substance	Intervention Arms				
	CBD + THC 12.50 mg	CBD + THC 18.75 mg	THC 12.50 mg	THC 18.75 mg	IP
Oil 1 THC Full-Spectrum (2.50 mg/mL THC)	4.81 mL	7.22 mL	5.00 mL	7.50 mL	-
Oil 2 Cannabis Full-Spectrum (50 mg/mL CBD + 1.83 mg/mL THC)	0.25 mL	0.37 mL	-	-	-
Oil 3 MCT (70% coconut 30% corn)	-	-	-	-	5 mL
Total (mL)	4.79 mL	7.19 mL	5.00 mL	7.50 mL	5 mL

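### Dose volume shows dose level to the researcher who gives the oil and collects the data, so the stated blinding fails for the high-versus-low and high-versus-placebo contrasts

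*Protocol article*

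**What the plan says.** - **Blinding claim.** Section 2 says: "This is a randomized controlled crossover clinical trial with a 1:1:1 allocation ratio, double-blinded". Section 2.3 closes with the aim: "Ensure allocation concealment and blinding of both participants and researchers".
- **Roles.** In Section 2.3, Evaluator 1 holds the allocation and is charged with "delivering the order in which the three bottles, identified by stickers on the bottom, will be applied by the second researcher (Evaluator 2"). Evaluator 2 is also the person "who will be responsible for applying the intervention protocols and collecting data". Evaluator 3 assesses the data after all stages.
- **Bottles.** "These bottles, containing the oil corresponding to the allocation group, will be numbered 1 to 3". On masking: "The contents of these bottles, identical in color and viscosity, will be known only to the researcher responsible for randomization (Evaluator 1").
- **Volumes.** Section 2.1 fixes the placebo: "In the placebo intervention, all participants will receive a dose of 5.00 mL of MCT". The last row of Table 1, in the order CBD + THC 12.50 mg, CBD + THC 18.75 mg, THC 12.50 mg, THC 18.75 mg, placebo, reads: "Total (mL) 4.79 mL 7.19 mL 5.00 mL 7.50 mL 5 mL". The MCT row is blank for all four active arms.
- **Administration.** In Section 2.4 the oil is handed over beforehand by the responsible researcher and given in drops to a participant wearing a blindfold and a nasal clip.

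**The concern.** Matching colour and viscosity hides which oil is in a bottle. It does not hide how much is given. If the larger volume is used only for high-dose sessions, whoever administers it knows the dose level before the IN and POST-IN recordings start, and that same person runs those recordings.

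The stated purpose of the trial is the dose–response relationship. High versus low and high versus placebo are the contrasts that carry it, and they are the ones that volume discloses. Knowledge of dose level could affect how loaded breathing is coached and how Borg scores are elicited. The placebo also matches the carrier volume of the low doses only, so the high-dose contrasts compare different amounts of oil as well as different amounts of cannabinoid. Neither problem can be removed in the analysis.

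**Working it through.** **Inputs.** Volumes of oil 1 (THC), oil 2 (cannabis) and oil 3 (MCT) by arm, and the printed totals, all from Table 1.

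**Step 1: reproduce the totals** (oil 1 + oil 2 + oil 3).

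| Arm | Components (mL) | Sum (mL) | Printed (mL) | Oils used |
|---|---|---|---|---|
| CBD + THC 12.50 mg | 4.81 + 0.25 | 5.06 | 4.79 | 2 |
| CBD + THC 18.75 mg | 7.22 + 0.37 | 7.59 | 7.19 | 2 |
| THC 12.50 mg | 5.00 | 5.00 | 5.00 | 1 |
| THC 18.75 mg | 7.50 | 7.50 | 7.50 | 1 |
| Placebo | 5 | 5 | 5 | 1 |

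Three totals reproduce and the two combination totals do not. That is a separate defect, so both sets are carried forward.

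**Step 2: group the arms by volume.**
- About 5 mL (4.79 to 5.06 under either set): CBD + THC 12.50 mg, THC 12.50 mg, placebo.
- About 7.5 mL (7.19 to 7.59 under either set): CBD + THC 18.75 mg, THC 18.75 mg.

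Even mixing the two sets, the smallest high volume exceeds the largest low volume by 7.19 − 5.06 = 2.13 mL. For THC alone the ratio is 7.50 / 5.00 = 1.5. The grouping is the same whichever totals are right.

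**Step 3: what volume alone reveals.** There are two groups. On 2 of 5 visits the dosing researcher knows the session is active and high dose. On the other 3, placebo and the two low doses stay pooled. This step needs no assumption about the bottles.

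**Step 4: if Evaluator 2 draws from the numbered bottles (not stated).** Only the combinations use two oils. Volume plus number of bottles gives four groups: each combination alone, THC 18.75 mg alone, and THC 12.50 mg together with placebo (both 5.00 mL from one bottle).

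**Step 5: if, in addition, bottle numbers stay constant (not stated).** The bottle used alone at 7.5 mL must be oil 1, its partner in the combinations must be oil 2, and the remaining bottle is oil 3. Of the 3! = 6 possible bottle-to-oil assignments, one fits a participant's five visits. All five interventions are then separable.

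**The case against.** **The oils may be combined in advance.** Section 2.1 does not say who combines them, and Section 2.4 refers to oil delivered beforehand. Preparation detail is commonly left to the full protocol. This stands against Step 4. Three numbered bottles for five interventions fit pre-mixing poorly but do not exclude it. It does not help Step 3: a pre-mixed dose of about 7.5 mL is still visibly larger than one of 5 mL to the person giving it, and Table 1 shows no top-up.

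**The bottle numbers may change.** The text says only that they run from 1 to 3. A reader might infer a fixed code that, once worked out, opens the whole trial, or conclude that three of the five interventions are certain to be identified. The documents support neither. Both rest on the unstated conditions in Steps 4 and 5.

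**The outcomes are largely instrumental.** Cardiac output, the main variable for sample size, comes from bioimpedance. The sEMG signal is software-processed and normalised to reference manoeuvres, with the PImax and MVV references recorded on the first morning before dosing. The valve load is set as a fixed share of each participant's PImax and PEmax, and Borg is secondary. This lowers the risk for cardiac output, and no bias in it has been shown. But sEMG sits under the primary outcome heading (Section 2.5.1), and muscle activity during loaded breathing still depends on how the participant breathes in a session run by Evaluator 2.

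**Evaluator 3 could remain blind.** That is true, and it protects the later assessment of the data. It cannot undo influence during collection.

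**Participants are masked and extra oil may not matter.** Whether blindfolded participants notice the volume is not established. Nor does anything in the article show that about 2.5 mL more oil changes the outcomes. The documents support only that carrier volume and dose move together in the design.

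**Conclusion.** The concern holds for dose level. As written, Evaluator 2 can tell both high-dose sessions (2 of 5 visits) from placebo and from the low doses. This follows from Table 1 and the fixed placebo volume alone, under either set of totals. It contradicts the stated blinding of researchers for high versus low and high versus placebo. Volume alone does not expose low dose versus placebo, or CBD + THC versus THC at the same level.

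The wider exposure is conditional. If Evaluator 2 draws from the bottles, only THC 12.50 mg and placebo remain alike. If the bottle numbers are also constant, nothing remains masked. The likely consequence is greatest for Borg ratings, effort-dependent loaded breathing and sEMG, and lower for cardiac output. The point should be fixed before dosing starts, because it affects the contrasts that the trial is built to estimate.

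**What to change.** - Evaluator 1, who already knows the allocation, prepares each session's complete dose in one opaque container labelled only with participant and visit.
- All five interventions are brought to one common volume with the MCT oil already in the study. The cannabinoid amounts are unchanged and the sponsor sets the volume.
- The bottle 1 to 3 code is dropped.
- If this is not done, the article should state that Evaluator 2 is not blinded to dose level and limit the double-blind claim accordingly.
- In either case, Sections 2, 2.1, 2.3 and 2.4 and Table 1 must be reconciled, including the two combination totals that do not equal their components.

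The cost is a few mL more oil in the lower-volume sessions and some preparation time for an existing team member. With equal volumes, the amount of oil no longer differs between dose levels.

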### 2.4. Study Design

After agreeing to participate in the study and signing the Informed Consent Form (ICF), data collection will begin over five days, during which the administration of CBD + THC, THC, both at two different dosages, or MCT oil, all will be evaluated in three stages: 1-Pre-Intervention (PRE-IN); 2-Intervention (IN); 3-Post-Intervention (POST-IN).

Because hemodynamic variables can be affected by medications, supplements, caffeine, smoking, and temperature [24,25], participants are asked to refrain from taking supplements for 72 h prior to the IN and to avoid exercise, caffeine, alcohol, and smoking for 24 h prior to the IN. In addition, the IN and POST-IN stages will always be performed in the same time period (afternoon) to avoid circadian influences.

The first day will be divided into two sessions: the morning session will include randomization, baseline assessment, and PRE-IN assessment. First, participants will be instructed to sit down and complete a self-administered 14-item Hamilton Anxiety Scale (HAM-A). Anthropometric data will then be collected by measuring the participant’s weight on a scale, height using a stadiometer, and blood pressure using an automated digital cuff.

Surface electromyography (sEMG) electrodes are placed on the respiratory muscles and remain in place throughout the data collection. Then, maximum inspiratory pressure (PImax) and maximum voluntary ventilation (MVV) assessments will be performed to normalize the electromyography data collected at all assessment stages. Baseline data will then be collected to characterize the sample, including spirometry and digital manometry to measure respiratory muscle strength (PImax and PEmax) and lung function.

Next, the PhysioFlow^®^ (Manatec Inc., Paris, France). electrodes will be placed, and the NIRS device will be attached to the participant, who will then be taken to bed to begin the pre-intervention stage (PRE-IN). In a semi-recumbent position with the trunk elevated at 45°, hemodynamics will be evaluated by electrical impedance through PhysioFlow^®^, respiratory muscle activity will be measured by Surface Electromyography (sEMG), and tissue oxygenation will be assessed via near-infrared spectroscopy (NIRS). After this evaluation stage, which will be used for comparison with the IN and POST-IN stages of the other interventions.

For all stages of respiratory Intervention (PRE-IN, IN and POS-IN) the data will be recorded for 8 min: 2 min of quiet breathing (QB), 2 min of breathing with inspiratory resistance at 30% of PImax and expiratory resistance at 10% of PEmax (VAL) using the BigBreathe^®^ valve (IMT/PEP, GHINNOTEK, Busan, Republic of Korea), followed by 4 min of recovery with spontaneous breathing (REC), as illustrated in Figure 1. During the 8 min of data collection, systolic blood pressure (SBP) and oxygen saturation (SaO_2_) will also be assessed, in addition to the Borg scale for mouth fatigue and dyspnea.

Except for the baseline stage, the other evaluation moments will take place exclusively in the afternoon. The study design can be better observed in Figure 2. Upon arriving at the research site, the participant will sit for the placement of electrodes and will then be taken to a bed, where they will be informed about the start of the pharmacological intervention. The respective oil, previously delivered by the responsible researcher following randomization, will be administered. Under the researcher’s guidance, the participant will be asked to wear a blindfold to cover their eyes and use a nasal clip to avoid any identification of the oil administered, open their mouth, and lift their tongue for the dose in drops. After the administration, the researcher will instruct the participant to remain seated and at rest. After 60 min, the second stage (IN) will take place and after 2 h and 30 min post-administration of the drug, the third evaluation stage (POST-IN) will begin.

The BigBreathe^®^ device will allow bidirectional threshold overload (IMT/PEP, GHINNOTEK, Busan, Republic of Korea) with an IMT range of 10–40 cmH_2_O and PEP of 5–20 cmH_2_O, with a resolution of 2 cmH_2_O. A variable load can be set on the IMT/PEP device, providing independent resistance to inspiration or expiration using two spring-loaded one-way valves. These valves only open when the pressure generated by the individual exceeds the spring tension set during inspiration and expiration, with simultaneous IMT and PEP effort in a single respiratory cycle [26]. A load of 30% of PImax and 10% of PEmax will be established for each participant, as previously described, as initial loads for respiratory muscle training, aiming only to activate the musculature while also considering the participant’s 45° trunk position.

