## Abstract

**Background/Objectives: ***Cannabis sativa* (CS) exerts its effects through the endocannabinoid system. Although studies have shown limited evidence regarding the plant’s therapeutic efficacy, little is known about the standardization of doses and their corresponding effects. This study aims to analyze changes in muscle electrical activity and cardiovascular hemodynamics before, during, and after administering doses of full-spectrum cannabis and tetrahydrocannabinol (THC) oils. **Methods:** Participants will be assigned to a single group that will undergo five different interventions: CBD + THC at 12.50 mg, CBD + THC at 18.75 mg, THC intervention at 12.50 mg, THC at 18.75 mg, and placebo intervention (PI). The study will enroll healthy, self-reported men and women aged 18 to 50, with no mental health disorders and no exposure to CS in the past six months. Interventions will occur on five randomized days, following three phases: (1) pre-intervention (PRE-IN); (2) intervention (IN)—1 h after oral oil ingestion; and (3) post-intervention (POST-IN)—2 h 30 min after ingestion. At each stage, 2 min of quiet breathing (QB); 2 min with an inspiratory resistance valve (30% of maximal inspiratory pressure—PImax) and expiratory valve (10% of maximal expiratory pressure—PEmax) (VAL); and 4 min of recovery without the valve (REC) were evaluated. Register: RBR-3jsvtbr. **Conclusions:** This study will enhance the understanding of the dose–response effects of full-spectrum cannabis and THC oils and may serve as a model for future research in this field.

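### PRE-IN is described only for the morning of day 1, after maximal respiratory manoeuvres, yet it serves as the comparator for afternoon stages; other text implies a PRE-IN for every intervention, and the two must be reconciled

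*Protocol article*

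**What the plan says.** **Detailed schedule (Section 2.4, Study Design).** On day 1, "the morning session will include randomization, baseline assessment, and PRE-IN assessment". Within that session the order is:

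1. anxiety scale and anthropometry;
2. sEMG electrodes;
3. manoeuvres: "Then, maximum inspiratory pressure (PImax) and maximum voluntary ventilation (MVV) assessments will be performed to normalize the electromyography data";
4. further tests: "Baseline data will then be collected to characterize the sample, including spirometry and digital manometry to measure respiratory muscle strength";
5. PhysioFlow and NIRS fitted, participant moved to bed, PRE-IN recorded.

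The PRE-IN recording is described as one "which will be used for comparison with the IN and POST-IN stages of the other interventions".

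**Time of day.** The same section states that "the IN and POST-IN stages will always be performed in the same time period (afternoon) to avoid circadian influences", and later that "Except for the baseline stage, the other evaluation moments will take place exclusively in the afternoon".

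**Visit at which oil is given (Section 2.4).** Arrival, electrodes, bed, oil, IN at 60 min, POST-IN at 2 h 30 min. No recording before the oil is mentioned.

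**Looser text.** The Abstract says "Interventions will occur on five randomized days, following three phases: (1) pre-intervention (PRE-IN"), then IN and POST-IN. The first paragraph of Section 2.4 likewise attaches three stages to the administrations over five days, and Section 2.3 lists PRE-IN among the stages of the intervention.

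**Analysis.** Sections 2.1 and 2.7 plan both intra-group and inter-group comparisons by GEE, with cardiac output as the main variable and a Sequential Bonferroni adjustment.

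**The concern.** The stated aim is change before, during and after dosing, so the PRE-IN value carries the word before. In the detailed schedule that value differs from the IN and POST-IN values in more than the drug. It is a morning value, whereas the later stages are held to the afternoon precisely to remove circadian influence. It follows a series of maximal respiratory efforts, whereas IN follows an hour at rest. For most interventions it also comes from another day with another electrode placement, and both primary measures (PhysioFlow and sEMG) are electrode-based.

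A systematic difference of this kind is not removed by GEE or by a multiplicity correction. It enters the intra-group estimate directly. A pre-dose recording that was never made cannot be recovered afterwards, so the point has to be settled before visits take place.

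**Working it through.** **1. Which reading does the text support?**

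| Place | What it implies about PRE-IN |
|---|---|
| Abstract; Section 2.3; first paragraph of Section 2.4 | One of three stages attached to the interventions; could mean every visit |
| Section 2.4, day-1 description | In the morning session of day 1, after the manoeuvres |
| Section 2.4, reuse sentence | One recording serves the stages of other interventions |
| Section 2.4, afternoon visit | No recording between electrode placement and oil |

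The detailed text favours a single PRE-IN. It does not say so outright, and the reuse sentence is grammatically incomplete.

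**2. What differs between PRE-IN and IN/POST-IN, if PRE-IN is taken only on day 1?**

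| Difference | Interventions affected, per participant |
|---|---|
| Clock time (morning against afternoon) | 5 of 5 |
| Preceding maximal manoeuvres | 5 of 5 |
| Day | 4 of 5 |
| Electrode re-placement | 4 of 5 |

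The count of four rests on one intervention being given in the second session of day 1, which five interventions over five days imply.

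**3. Effect on the two kinds of comparison.** Let δ be the combined systematic shift and τ_a the effect of intervention a.

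- Intra-group: E(IN_a − PRE) = τ_a + δ. For placebo the expectation is δ.
- Between interventions: (IN_a − PRE) − (IN_b − PRE) = IN_a − IN_b. PRE drops out exactly, so there is no bias, but also no day-specific adjustment.

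**4. Size, as an illustration.** The article gives no sample size, shift or SD, so it has no figure to reproduce. Assumed inputs: n = 20, cardiac output shift 0.25 to 0.5 L/min, within-participant SD 0.4 to 0.8 L/min, τ = 0. The SD of a paired difference is SD × √2, so the noncentrality is shift / (SD × √(2/n)) on 19 degrees of freedom. For example, shift 0.5 and SD 0.6 give 0.5 / (0.6 × √0.1) = 2.635. The critical values are 2.093 (two-sided 0.05) and 3.174 (two-sided 0.005).

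| Shift (L/min) | SD (L/min) | Noncentrality | P(reject), 0.05 | P(reject), 0.05/10 |
|---|---|---|---|---|
| 0.25 | 0.4 | 1.976 | 0.47 | 0.15 |
| 0.25 | 0.6 | 1.318 | 0.24 | 0.05 |
| 0.25 | 0.8 | 0.988 | 0.16 | 0.03 |
| 0.5 | 0.4 | 3.953 | 0.96 | 0.77 |
| 0.5 | 0.6 | 2.635 | 0.71 | 0.33 |
| 0.5 | 0.8 | 1.976 | 0.47 | 0.15 |

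The last column takes the first Sequential Bonferroni step over ten tests (five interventions × two contrasts with PRE-IN). The article does not define the family, so ten is also an assumption.

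**5. Simulation check.** Five inert conditions, n = 20, 20,000 runs, shift of 0.5 SD of the paired difference, unadjusted 0.05. With the shared PRE-IN, each pre-to-post test rejects in about 57% of runs, placebo included. With a baseline under the same conditions before each dose it rejects in about 5%. The active-minus-placebo contrast rejects in about 5% either way.

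**6. Precision forgone between interventions.** A same-day baseline used as covariate removes a fraction ρ² of the residual variance. For an assumed within-participant correlation of 0.5 to 0.7 this is 0.5² = 25% to 0.7² = 49%.

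**The case against.** **PRE-IN may be intended at every visit.** Three places list it among the stages of the interventions, the design figure is not available here, and Section 2.4 names the baseline assessment and PRE-IN as separate items while exempting only the baseline stage from the afternoon. This stands as far as it goes: a reader might infer that one PRE-IN is settled fact, and the text does not establish that. It does not remove the problem, because staff who follow the detailed visit description would make no pre-dose recording.

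**The randomised comparison is sound.** This stands in full. Placebo is one of the five interventions, the order is randomised, and the common PRE-IN cancels. A reader might infer that the trial's drug-versus-placebo results are invalid; they are not. The cost there is precision only, and a crossover analysed by same-stage contrasts is valid without period baselines.

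**Nobody says the shift will be called a drug effect.** Also correct. A reader might infer that a PRE-IN to IN change under one active oil will be reported as pharmacological, but no sentence commits to that, and the placebo arm would show the same shift. What remains is that intra-group tests are planned and nothing restricts their reading.

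**The probabilities rest on assumed inputs.** They do. The unadjusted range of 0.16 to 0.96 also ignores the planned Sequential Bonferroni correction; the adjusted range is lower but still reaches 0.77.

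**Prior exertion may have worn off.** Fitting PhysioFlow and NIRS takes some time before PRE-IN, and no interval is given. Its contribution is therefore unknown, possibly small. Clock time does not depend on it.

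**Conclusion.** The point holds in a limited form. The article is inconsistent on when PRE-IN is recorded, and its detailed schedule describes it only on the morning of day 1, against the article's own reason for keeping the other stages in the afternoon. If that schedule is followed, intra-group PRE-IN versus IN or POST-IN differences cannot be attributed to the oil.

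The direction and size of the shift cannot be derived from the document. The rejection probabilities show sensitivity under assumed n, shift, SD and test family; they are not estimates for this trial. The possible 25% to 49% reduction in residual variance likewise depends on an assumed correlation.

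**What to change.** First, make the Abstract, Section 2.3 and Section 2.4 say the same thing about when PRE-IN is recorded. Then choose one of two routes.

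1. **Preferred.** Record the same 8-min sequence each afternoon, after electrode placement and before the oil, and enter that day's PRE-IN as a covariate for that day's IN and POST-IN. Cost: about 8 min per visit, with electrodes already attached, plus wording.
2. **If visits cannot change.** State that the day-1 PRE-IN is descriptive, that drug effects are judged only as intervention minus placebo at the same stage (IN or POST-IN), and that no intra-group PRE-IN comparison will support a claim of effect. Cost: wording only. The between-intervention contrasts remain valid but without day-specific baseline adjustment.
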